## Abstract

**Background:**

Despite substantial investment in detection, early intervention and evidence-based treatments, current management strategies for diabetes-associated retinopathy and cardiovascular disease are largely based on real-time and face-to-face approaches. There are limited data re telehealth facilitation in type 2 diabetes management. Therefore, we aim to investigate efficacy of telehealth facilitation of diabetes and cardiovascular disease care in high-risk vulnerable Aboriginal and Torres Strait Islanders in remote/very remote Australia.

**Methods:**

Using a pre-post intervention design, 600 Indigenous Australians with type 2 diabetes will be recruited from three primary-care health-services in the Northern Territory. Diabetes status will be based on clinical records. There will be four technological interventions: 1. Baseline retinal imaging [as a real-time patient education/engagement tool and telehealth screening strategy]. 2. A lifestyle survey tool administered at ≈ 6-months. 3. At ≈ 6— and 18-months, an electronic cardiovascular disease and diabetes decision-support tool based on current guidelines in the Standard Treatment Manual of the Central Australian Rural Practitioner’s Association to generate clinical recommendations. 4. Mobile tablet technology developed to enhance participant engagement in self-management. Data will include: Pre-intervention clinical and encounter-history data, baseline retinopathy status, decision-support and survey data/opportunistic mobile tablet encounter data. The primary outcome is increased participant adherence to clinical appointments, a marker of engagement and self-management. A cost-benefit analysis will be performed.

**Discussion:**

Remoteness is a major barrier to provision and uptake of best-practice chronic disease management. Telehealth, beyond videoconferencing of consultations, could facilitate evidence-based management of diabetes and cardiovascular disease in Indigenous Australians and serve as a model for other conditions.

**Trial registration:**

Australia and New Zealand Clinical Trials Register (ANZCTR): ACTRN 12616000370404 was retrospectively registered on 22/03/2016

## Background

Diabetes and cardiovascular disease (CVD) are leading causes of personal and healthcare system disease burden, globally [1], and in Australia [2]. It is anticipated that this burden will disproportionately affect vulnerable populations, such as those in low-income countries and Indigenous populations [3], particularly in remote settings.

A wide range of interventions aimed at improving chronic disease outcomes and reducing care costs has been tried. These interventions mostly fall into one of two categories. One aspect is quality-improvement that focuses on service delivery in primary care and support services for patient self-management. The other aspect is patient-based disease-management. Evidence suggests the interventions that not only target disease management, but also aim to improve care-delivery design may be more effective than those that target disease management alone [4, 5]. Targeted e-health applications that facilitate both service delivery and disease management have potential to meet such an objective. To date, clinical e-health applications mainly relate to the use of electronic health record systems (often alongside older paper-based systems), telecommunication of medical reports and videoconferencing consultations between a clinician and patient.

Telehealth is, in the context of the present study, that area of e-health that centres on the provision of health-related services and information using telecommunication-based technologies. Telehealth in the clinical setting is in its infancy in Australia [6], where the use of this term has been largely limited to one Federal government funded health-related service — that of a videoconferencing consultation between a specialist clinician and patient, subject to specific criteria [7]. By contrast, global uptake of a broad spectrum of e-health technologies, particularly mobile-health, is high [8].

Telehealth facilitation of service delivery and disease management has the potential to improve health outcomes for people with diabetes and to improve the quality of service delivery in the primary care setting. Currently, there are inadequate data to support the widespread clinical uptake of telehealth technologies. Therefore, the ‘Telehealth Eye and Associated Medical Services Network’ [TEAMSnet] study aims to address the knowledge gaps in three areas — telehealth facilitation of 1. diabetic retinopathy screening 2. evidence-based diabetes and CVD management (via decision support and survey tools) and 3. patient self-management strategies.

This paper presents the protocol for the TEAMSnet study. This technology-based pre-post intervention study aims to describe the baseline characteristics of the participants with diabetes and clinical workflows in partner health service and to investigate the impact of telehealth facilitation in the management of CVD, diabetes and diabetic retinopathy. We hypothesise that telehealth facilitation of diabetes management will lead to improvements in patient engagement [attendance rates and survey participation] and clinical outcomes, such as blood pressure and metabolic control.

## Methods/Design

### Study design

This is a pre-post study of technology-facilitated management of diabetes, CVD, and diabetic retinopathy. We plan to enrol 600 adults (age ≥18 years) with clinically-diagnosed diabetes from three remote Northern Territory Aboriginal-controlled health services — Central Australian Aboriginal Congress [CAAC] in Alice Springs, Miwatj Health Aboriginal Corporation [Miwatj] that incorporates the four clinics at Nhulunbuy, Galiwin’ku/Elcho Island, Yirrkala, Gunyangara/Ski Beach in East Arnhem Land and Wurli-Wurlinjang Health Service [Wurli] in Katherine. Recruitment and intervention are anticipated to occur over a 3-year period. Participants will receive retinal imaging, diabetic retinopathy screening, including diabetes education, at baseline, followed by lifestyle assessment six months later, including self-management support. An electronic CVD and diabetes decision support tool that includes an Indigenous-specific CVD risk calculator, based on best-practice as generally defined by guidelines in the current Standard Treatment Manual of the Central Australian Rural Practitioner’s Association [CARPA], will be developed in conjunction with a clinical working group and used to generate a clinical recommendations report to assist clinicians with evidence-based management of CVD, diabetes and diabetic retinopathy approximately 6–18 months after baseline. Mobile tablet technology based on clinical input and feedback will be developed to support clinical staff and participants with engagement in diabetes management and self-management, respectively.

### Study aims and objectives

The overarching aim of the TEAMSnet project is to improve health care, and therefore health outcomes, for Indigenous Australians in under-resourced communities through the integration of existing electronic health record systems, specifically Communicare™ (Healthconnex, Perth, Australia), with the customisable, web-based health information technology called Chronic Disease Management Platform [CDMP], an existing, licence-free platform that thereby facilitates sustainability. A secondary aim is to evaluate the cost-efficacy of the intervention. There are three main objectives under the broad aim.
*Telehealth facilitation of clinical management* via *CVD and diabetes electronic decision support and remote image-based diabetic retinopathy assessment*
Our first objective is to make it easier for treating doctors to adhere to relevant evidence-based guidelines, specifically the current Standard Treatment Manual of the Central Australian Rural Practitioner’s Association (CARPA) [9] and the 2008 NHMRC Guidelines for the Management of Diabetic Retinopathy [10]*,* prepared by the Australian Diabetes Society. To this end, (1) CARPA guidelines are being encoded into a CARPA_CVD and diabetes electronic decision support application [EDS] that sits within CDMP. In addition, evidence-based diabetic retinopathy management has been made easier for primary care practitioners via (2) the development of a second application, Global Retinal Imaging [GRI], that interfaces with the widely–used Centervue DRS and Canon CR-2 non-mydriatic retinal cameras and stores the captured digital retinal and external eye images. These imaging, grading and reporting data are accessible from within CDMP to both certified retinopathy graders [for grading diabetic retinopathy level and generating retinopathy reports based on 2008 Australian NHMRC diabetic retinopathy management guidelines] and to authorized medical and eyecare practitioners [to view and compare ocular images and retinal status over time, thereby facilitating continuity of care].
*CDMP-based facilitation of shared clinical information, such as login access to CDMP-stored retinal images for ophthalmologists and optometrists*
Our second objective is to improve the timely exchange of relevant health information and the communication between a patient’s health care providers. CDMP facilitates this through use of a unique practitioner access code that enables a specialist medical practitioner, such as an optometrist or ophthalmologist, to view only relevant patient data, including reports.
*Improve engagement of patients in self-care, particularly adherence to clinical visits*
Our third objective is to improve engagement of patients in self-care. GRI retinal imaging will provide both a powerful education and retinopathy assessment opportunity. In addition, a third technology, (3) a custom-built e-mobile health device in the form of a tablet with viewable clinical data, GRI images and educational content, developed with clinical and Aboriginal Health Worker input, will facilitate health worker communication with patients between medical consultations and is aimed at improving relationships and engaging patients in self-care. A fourth application, (4) a suite of lifestyle surveys and a related reporting template based on CARPA recommendations for smoking, nutrition, alcohol, physical activity and emotional well-being [SNAPE] has been developed and is accessible via CDMP in a clinical setting or via the mobile tablet application anywhere. This is designed to be both a patient engagement and clinical management tool that facilitates the measurement, goal-setting and monitoring of important lifestyle risk factors for CVD, diabetes and diabetic retinopathy. All three telehealth reports, EDS, GRI and SNAPE, will be accessible via either the EHR [Communicare] or CDMP.

Apart from the development and implementation of the four technologies, the primary outcome includes improved adherence to clinical care, such as eyecare visits. Secondary outcomes include reduction in hospitalizations and cost-efficacy of the suite of technologies, both individually and collectively.

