**Fig. 5 Fig5:**
[figure not shown]
SNAPE lifestyle survey reportEDS development, use and reporting protocolOnce partner sites were identified, we identified the CARPA standard treatment manual as the most appropriate guideline for CVD and diabetes EDS development. As Communicare is the EHR system used by all partner sites, ideally the TEAMSnet EDS application would need to be interfaced with Communicare for automated syncing of as much of the clinical data required by EDS as possible so as to avoid duplication and improve clinical efficiency. The developers of the CARPA standard treatment manual and Communicare were advised of the TEAMSnet project and agreed to support the project informally as advisors and collaborators, particularly in relation to timing of their product updates and releases. In return, TEAMSnet would provide both organisations with potentially useful user feedback during the project.TEAMSnet EDS will provide clinicians with three CVD and diabetes management tools.The **CVD risk calculator and slide rule** that enables baseline measurement and regular monitoring of a participant’s overall CVD risk (Fig. 6).The **detailed CVD and diabetes risk-analysis tool** that provides a clinician with specific recommendations and optional learning points for best-practice management of a participant’s CVD risk (Fig. 7).
**Active CVD and diabetes decision-support tool** — a proactive clinical process whereby each recommendation is reviewed by the clinician and either accepted or rejected, in which case a textbox appears for the explanation. An EDS report will be generated for each participant as soon as possible after the second clinical visit [at which surveys are administered]. A second and final EDS report will be generated for participants prior to the end of the study (Fig. 8).

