## Data analysis

Investigators and their supporting statistics departments will conduct data analysis. Site differences will be analysed. Analyses will provide important descriptive data, such as prevalence rates and lifestyle data, proportion treated to target for CVD, diabetes and diabetic retinopathy risk factors and predictors of diabetic retinopathy and CVD outcomes. Analysis of covariance (ANCOVA) will be used to compare differences between groups. To assess confounding, covariates will include age, gender, and established and emerging risk factors for CVD, diabetes and diabetic retinopathy, as appropriate. Non-parametric statistics will be used when assumptions for parametric methods are violated. All tests will be conducted using an alpha level of 0.05 and 95% confidence intervals will be reported.

Complete case analysis and, where reasonable, multiple imputation will be employed for the management of missing data. Missing data may occur due to drop-out, missed assessments or item non-response. With knowledge of the missing data mechanism, all available information can be used. One approach will be to use the multilevel model, a full-likelihood method that allows for a response to be missing at random, where missingness depends only on observed data and not on unobserved data. Another strategy involves imputing missing values by multiple imputation procedures.

The proposed economic evaluation aims to include pre- and post-study resource utilization costs for both the costs and consequences and a cost consequence analysis (CCA). Standard unit costs i.e. Australian Medicare Benefits Schedule will be applied to the resource-use data. Costs will be presented in total and disaggregated forms, such as those from different sectors — the health sector, patients and government.

Of the recruitment target of 600 Indigenous Australians with diabetes, to date 576 participants have been recruited and undergone retinal imaging for diabetic retinopathy screening.

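### The single-group pre-post design cannot give a credible cost-efficacy figure for each technology individually, and the economic method is named in two incompatible ways

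*Protocol article*

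**What the plan says.** **Outcome.** At the end of Study aims and objectives, the secondary outcomes include the "cost-efficacy of the suite of technologies, both individually and collectively".

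**Design.** Study design states: "This is a pre-post study of technology-facilitated management of diabetes, CVD, and diabetic retinopathy". No concurrent control is described, and no staggered or randomised introduction of components.

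**Timing of the four technologies.**
- Imaging and survey (Study design): "Participants will receive retinal imaging, diabetic retinopathy screening, including diabetes education, at baseline, followed by lifestyle assessment six months later".
- EDS (EDS development, use and reporting protocol): "An EDS report will be generated for each participant as soon as possible after the second clinical visit [at which surveys are administered". Then: "A second and final EDS report will be generated for participants prior to the end of the study". Study design places the EDS recommendations at roughly 6 to 18 months after baseline. The abstract gives about 6 and 18 months.
- Tablet (abstract, Methods): encounter data are opportunistic. No time point or allocation rule is given.

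**Economic evaluation.** The abstract says: "A cost-benefit analysis will be performed". Data analysis says that the evaluation aims to include "pre- and post-study resource utilization costs for both the costs and consequences and a cost consequence analysis (CCA". Study aims and objectives and the Discussion use a third term, cost-efficacy. Resource use is described as pre-study and post-study (Data collection and outcome measures; Data analysis).

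**The concern.** A cost-efficacy figure for one technology needs two things: its cost, and the change in outcome that is due to it. The cost can be recorded. The effect needs some contrast between having and not having that technology, other things being equal, and the described design supplies none for imaging, survey or EDS. For the tablet, the only contrast is between users and non-users. They are likely to differ in engagement, and engagement is what the primary outcome (adherence to clinical appointments) is meant to mark.

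Health services may use such results to decide which tool to keep. A per-technology figure from these data could reflect the order of the visits, a background trend or who chose to use the tablet.

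The two method names lead to different products. A cost-benefit analysis values outcomes in money and gives a net figure. A cost-consequence analysis sets costs and outcomes side by side without combining them. A reader of the abstract would expect a result that the analysis section does not plan to produce.

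**Working it through.** The plan gives no figure to reproduce, because the question is whether the quantity can be estimated. I checked this through the rank of the design matrix.

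**Model.** Mean outcome = b0 + bG·G + bS·S + bE·E + bT·T, where G, S, E and T are 1 once imaging, survey, EDS and tablet are in use. A coefficient is estimable only if its unit vector lies in the row space of the design matrix. The 0/1 patterns follow the schedule above.

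| Setting | Rank / parameters | Separately estimable |
|---|---|---|
| (a) Pre (0,0,0,0), post (1,1,1,1) | 2 / 5 | none; only bG+bS+bE+bT |
| (b) As (a), tablet used by some | 3 / 5 | tablet; otherwise only bG+bS+bE |
| (c) Pre, months 0–6, after month 6; no time effect | 4 / 5 | imaging, tablet; otherwise only bS+bE |
| (d) As (c) plus linear trend | 4 / 6 | tablet |
| (e) As (c) plus period effects | 4 / 7 | tablet |

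In (b) to (e) the tablet contrast is user versus non-user, so it is self-selected. In (c) imaging separates only because a background trend is assumed absent.

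**Finer data.** The abstract lists encounter-history data, so monthly periods are conceivable. I assumed 12 months before and 18 months after baseline and left the tablet out.

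| Setting | Rank / parameters | Separately estimable |
|---|---|---|
| (f) Linear trend, EDS at the survey visit | 4 / 5 | imaging; otherwise only bS+bE |
| (g) Linear trend, EDS 3 months after the survey | 5 / 5 | imaging, survey, EDS |
| (h) Free month-since-enrolment effects, EDS 3 months after | 30 / 33 | none |

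**Staggered entry.** Study design spreads recruitment and intervention over 3 years. I assumed 12 entry dates three months apart and a free effect for each calendar month, which gives 66 parameters. The rank is 65 with EDS at the survey visit (imaging separable, survey and EDS not) and 66 with a 3-month lag (all three separable).

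**Reading.** Settings (f), (g) and the staggered case buy separation with assumptions: each effect is an immediate, lasting step; the effects add up; and nothing else changes with time since enrolment. Setting (h) shows that a free effect of time since enrolment removes every component. Additivity is itself doubtful, since Mobile tablet application says that the tablet displays data from the other three tools and can deliver the surveys. If the survey-to-EDS lag varied between participants, that variation would be unallocated and would probably follow attendance and clinic workflow.

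**Economic method.** No arithmetic applies. The abstract names cost-benefit analysis and Data analysis names cost-consequence analysis. Both are current text, and one analysis cannot be both.

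**The case against.** Four arguments deserve an answer.

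1. *The components are not perfectly aliased.* A reader might infer from the schedule that survey and EDS are perfectly correlated and that everyone receives all four tools in one fixed order. The documents do not support that. The first EDS report comes as soon as possible after the survey visit, not at it; Study design gives a window of about 6 to 18 months; and tablet use is opportunistic. With a lag, the effects can be algebraically estimable, as (g) shows. This stands, and the point is confined to confounding. It does not make the estimates credible, because the separation rests on assumed trends and on unallocated timing.

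2. *Cost-efficacy need not mean a causal ratio.* The article does not define it so. A cost-consequence analysis can list each tool's cost beside its own products: retinopathy detected, recommendations accepted or rejected, survey referrals. This also stands, and the fix keeps these results. But the stated outcome does not limit itself to description, and the Discussion promises evidence on efficacy and cost-efficacy.

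3. *Detail may sit in an analysis plan.* A plan can specify a model or a costing inventory. It cannot supply a comparator that the design lacks. For costing the argument does hold. A reader might infer that cameras, grading, software and tablets are left out because only resource-use costs are named. Data analysis says only what the evaluation aims to include, and it mentions costs to patients and government, so omission of programme costs cannot be concluded.

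4. *The method mismatch is one term in an abstract.* It is minor and easily corrected, but it is a real contradiction.

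**Conclusion.** The point holds for the individual part of one secondary outcome. Of four technologies, none has an individual effect that the described design can separate from the other tools, from time or from self-selection without strong assumptions. In the plain pre-post comparison, only the sum of the four is estimable. The collective change can be estimated as a pre-post difference, subject to the usual limits of an uncontrolled design. The primary outcome is not touched by this point.

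The conclusion rests on the article's account of a single group, with imaging, survey and EDS scheduled for all participants and no allocation rule for the tablet. The conflict between cost-benefit and cost-consequence analysis is a separate, smaller inconsistency of terms. The change should be made before analysis.

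**What to change.** - In Study aims and objectives, restrict the secondary outcome to the costs and consequences of the suite collectively.
- Report each technology's cost, uptake and process yield (for example retinopathy detected, EDS recommendations accepted, survey referrals) descriptively, without attributing an individual effect.
- Label any comparison by period or by tablet use as exploratory and non-causal. A comparison of months 0–6 with months 6–18 should not be presented as a component effect: it sets imaging alone against imaging carry-over plus survey plus EDS, over windows of 6 and 12 months, and is confounded with time.
- In the abstract, replace cost-benefit analysis with the cost-consequence analysis of Data analysis. Where the aims and Discussion say cost-efficacy, state that this analysis is meant.

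**Cost.** A narrower claim and a wording amendment. Data analysis reports 576 of 600 participants already recruited and imaged, so adding a comparator is unrealistic. Changing a stated secondary outcome at that stage should be dated and explained, and the registry entry aligned if it carries the same wording. The changes require no new data on participants.
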